## Abstract

**Background:**

As a common clinical symptom that often bothers midlife females, migraine is closely associated with perimenopause. Previous studies suggest that one of the most prominent triggers is the sudden decline of estrogen during perimenopausal period. Hormone replacement therapy (HRT) is widely used to prevent this suffering in perimenopausal women, but effective diagnostic system is lacked for quantifying the severity of the diseaase. To avoid the abuse and overuse of HRT, we propose to conduct a diagnostic trial using multimodal MRI techniques to quantify the severity of these perimenopausal migraineurs who are susceptible to the decline of estrogen.

**Methods:**

Perimenopausal women suffering from migraine will be recruited from the pain clinic of our hospital. Perimenopausal women not suffering from any kind of headache will be recruited from the local community. Clinical assessment and multi-modal MR imaging examination will be conducted. A follow up will be conducted once half year within 3 years. Pain behavior, neuropsychology scores, fMRI analysis combined with suitable statistical software will be used to reveal the potential association between these above traits and the susceptibility of migraine.

**Discussion:**

Multi-modal imaging features of both healthy controls and perimenopausal women who are susceptible to estrogen decline will be acquired. Imaging features will include volumetric characteristics, white matter integrity, functional characteristics, topological properties, and perfusion properties. Clinical information, such as basic information, blood estrogen level, information of migraine, and a bunch of neurological scale will also be used for statistic assessment. This clinical trial would help to build an effective screen system for quantifying the severity of illness of those susceptible women during the perimenopausal period.

**Trial registration:**

This study has already been registered at Clinical Trials. gov (ID: NCT02820974). Registration date: September 28th, 2014.

## Background

As a common headache disorder, migraine is characterized by recurrent headache attacks accompanied with symptoms including nausea and vomiting [1]. According to the World Health Organization (WHO), migraine is considered as one of the most disabling and burdensome diseases [2, 3]. In general, adult females experience migraine attacks twice more than males, and although men and women reported similar headache severity and frequency, women reported more migraine related symptoms [4, 5].

This gender difference is mainly caused by the difference in sex hormone. Estrogen quantities are relatively stable in men and undergo a much more gradual decline with age as compared with women [6]. For example, previous studies revealed that migraine is closely linked to the menopausal period of women, and one of the most prominent triggers is the sudden decline of estrogen [7–9]. Estrogen can bind to its receptors of nucleus or cytoplasm in the brain, and then exert its function of pain transmission by gene transcription and protein synthesis [10]. However, this procedure would be disturbed by the sudden drop of estrogen in perimenopausal period, which would furtherly result in the susceptibility to migraine [6].

Since the decline of estrogen begins in perimenopausal period, giving hormone replacement therapy (HRT) in this period is considered as an effective method to treat migraine [11, 12]. To avoid the abuse and overuse of HRT which could cause some severe unpleasant complications, those women should be given the lowest effective dose of medication [13, 14]. However, headache is a subjective feeling, and effective diagnostic system is still lacked for quantifying the degree of migraine, which could result in the abuse and overuse of HRT in treating this disease.

In the past two decades, functional magnetic resonance imaging (fMRI) technique has become an indispensable tool in migraine research and has greatly contributed to our understanding of migraine pathophysiology [15–17]. It could show anatomic and functional cerebral transformations associated with the clinical evolution and could be applied to most individuals without adverse effects. Maleki et al. found that female migraineurs have thicker posterior insula and precuneus cortices as compared with both male migraineurs and healthy controls of both sexes [18]. Compared to healthy controls, Kim and colleagues revealed a reduction of gray matter (GM) density in migraineurs, including insula, motor/premotor, prefrontal, cingulate, posterior parietal, and orbitofrontal cortex [19]. Huang et al. found reduced fractional anisotropy (FA) in the right frontal of migraine patients by using a tract-based spatial statistics (TBSS) method, which means the microstructure of white matter (WM) in that region is impaired [20]. Liu et al. found that the resting-state functional connectivity (FC) was disrupted in patients with long-term migraine through the method of graph theory [21]. However, these researches are all focused on both male and female patients at all ages, which contributes little to quantify the degree of migraine in perimenopausal women. According to our knowledge, no previous studies had researched the imaging abnormality of perimenopausal women who are susceptible to the decline of estrogen. Since estrogen plays a pivotal role in pain transmission in our brain [10], we thus raised the current hypothesis that brain structure and function of these women who are susceptible to estrogen drop exhibit unique characteristic changes in multi-modal images.

Consequently, we would like to conduct a prospective clinical trial to investigate the imaging abnormalities in these susceptible perimenopausal women. At the beginning, perimenopausal women around who had migraine will be recruited from the pain clinic of our hospital. Perimenopausal women around who did not have migraine will be recruited as healthy controls (HC) from the local community. Then, these subjects will undergo a series of multi-modal MRI brain scans and neuropsychology scales to assess the mental and physical state of these subjects. Multi-modal MR images of these two groups of subjects will be compared to find significant features as objective biomarkers.

## Methods

The flowchart of the current trial is described in Fig. 1.

**Fig. 1 Fig1:**
[figure not shown]
The flowchart of the current trial

### Subject

All subjects will be provided informed, written consents after the study procedure has been fully explained in detail. Females who match the following criteria would be included in the migraine group: (1) age ranges from 40 to 55 years old; (2) irregular menstrual cycle; (3) suffered from migraine; (4) normal neurological examination. Females who match the following criteria would be included in the HC group: (1) age ranges from 40 to 55 years old; (2) irregular menstrual cycle; (3) not suffered from any kinds of headache; (4) normal neurological examination. Exclusion criteria will be as follows: (1) severe psychiatric disorders, such as dementia, episode, epilepsy, major depression; (2) significant neurological illness, such as significant head trauma, tumor, meningitis or central nervous system (CNS) inflammatory lesions and vascular complications clues; (3) any MRI contraindications; (4) alcohol, nicotine or drug abuse.

Sample size have been estimated by referring to other studies [22, 23]. A sample size of 40 patients per group will be suitable for a power of 0.8 and an alpha significance level of 0.05 (two-side). Considering the drop-out ratio (25%) and unqualified images of included subjects, the total sample size is 55 in each group.

### Clinical assessments

Demographic and clinical features of all subjects will be collected and recorded, such as age, education level, body mass index (BMI), occupation and menstrual cycle. All participants will receive the following battery of neuropsychological tests: Montreal Cognitive Assessment (MoCA) and Mini-mental State Examination (MMSE) will be used to assess the mental state of subjects. The Short Form health survey (SF-36) will be applied to evaluate the quality of life, and Self-rating Depression Scale (SDS) and Self-rating Anxiety Scale (SAS) will be performed to measure the severity of self-reported depression and anxiety. Migraine will be diagnosed according to the International Headache Society (IHS) criteria of the International Classification of Headache Disorders (ICHD-3 beta version) [1]. The following data will be collected from migraine participants: (1) type of migraine (migraine with aura, migraine without aura, etc.), (2) frequency of migraine attacks, (3) duration of migraine attacks, (4) headache location (unilateral or bilateral), (5) Migraine Disability Assessment Scale (MIDAS) score (the score is divided into 4 grades, higher grade means more severer disability). Blood samples were drawn at the screening centers and processed within 2 h according to a standardized protocol to assess the hormone level [24].

### Follow up

A follow up will be conducted within three years after individual’s first visit. Individuals will come back to the medical center once half year for countercheck, and all the protocols and evaluations will be the same as that they get at the first time. In addition, medication type and dose will also be recorded.

### Multi-modal MRI examination

Multi-modal imaging examination will be performed with a 3.0-T MRI system (MR750; GE Healthcare, Milwaukee, WI, USA) using an 8-channel head coil array with foam padding to restrict head motion. Multi-modal scans including high-resolution three-dimensional brain volume T1-weighted imaging (T1WI), diffusion kurtosis imaging (DKI), resting-state blood oxygenation level-dependent (RS-BOLD) imaging and three-dimensional pseudo-continuous arterial spin labeling (3D-pCASL) imaging will be conducted to detect microstructural and functional properties. All the sequences we mentioned will use the isotropic spatial resolution.

#### High-resolution T1WI

Sagittal three-dimensional brain volume (3D-BRAVO) sequence will be used for the acquisition of high-resolution T1-weighted images, according to the following parameters: echo time (TE) = 3.2 ms, repetition time (TR) = 8.2 ms, TI = 450 ms, flip angle (FA) = 12°, field of view (FOV) =256 × 256 mm^2^, matrix = 256 × 192, slice thickness = 1.0 mm, slice number = 166. The whole procedure will cost 4 min 43 s.

#### DKI

DKI datasets will be collected using a douple-spin-echo diffusion tensor echo planar imaging (SE-SS-DT-EPI) sequence with a clinically oriented protocol. The acquisition parameters are as follows: six-b-values of 0,500, 1000,1500, 2000, and 2500 s/mm^2^, 10 b_0_ images, 30 diffusion gradient directions, TR = 6500, TE = 108 ms, FOV =256 × 256 mm^2^, matrix = 128 × 128, slice thickness = 3 mm, FA = 90°, slice number = 50, voxel size = 2 mm × 2 mm × 5 mm. The acquisition time for this protocol will be 6 min.

#### RS-bold

RS-BOLD images will be collected using a gradient-recalled echo-planar imaging (GRE-EPI) sequence with the following parameters: TR = 2000 ms, TE = 40 ms, FA = 90°, slice number = 36, inter slice gaps = 0 mm, FOV = 240 × 240 mm^2^, matrix = 64 × 64, slice thickness = 3 mm, in-plane spatial resolution = 3 × 3 mm^2^. Participants will be reminded to lie quietly in the scanner with their eyes closed and thinking nothing during data acquisition. The whole procedure will cost 6 min 10 s.

#### 3D-pCASL

Resting-state perfusion imaging was performed using pCASL sequence with a 3D fast spin-echo acquisition and background suppression: TR = 5046, 11.1 ms, FOV = 128 × 128 mm2, matrix = 128 × 128 mm2, slice thickness = 3 mm, FA = 111°, number of excitation = 3, no gap; 40 axial slices; number of excitation = 3. The whole procedure will cost 4 min 53 s.

### Imaging data processing

#### High-resolution T1WI data

All T1 imaging data will be processed and examined for voxel-based morphological (VBM) analyses using the VBM8 toolbox (http://dbm.neuro.uni-jena.de/vbm/) in Statistical Parametric Mapping (SPM) (SPM8, Wellcome Department of Imaging Neuroscience Group, London, UK; http://www.fil.ion.ucl.ac.uk/spm) running in MATLAB 2014a platform. We will perform an optimized VBM protocol in which a brain-tissue-only template will be used other than a whole-brain template. Brain Extraction Tool (integrated in MRIcro; http://www.mricro.com) was used to remove non-brain region images [25]. After removal of nonbrain regions, images will be segmented into GM, white matter (WM), and cerebrospinal fluid (CSF) by using the Diffeomorphic Anatomical Registration Through Exponentiated Lie algebra (DARTEL) algorithm [26]. Afterward, the normalized images would be averaged by using SPM mean function. To create the final template, all average images would be smoothed using an isotropic Gaussian kernel with a full width at half maximum (FWHM) of 8 mm.

#### DKI data

All DKI images will be processed using a combination of FMRIB’s Software Library (FSL) [27] and in-house image processing tools developed in MATLAB. The diffusion dataset will be modulated to get potential 3D head motion and eddy current distortion using FSL eddy correct. The toolbox implement in MTALAB will be applied to deal with diffusional kurtosis tensors. Region of interest (ROI) of headache will be drawn by hand. DKI parameters of migraine pain-ROIs, such as mean kurtosis (MK), mean diffusivity (MD) and fractional anisotropy (FA), will be measured. All feature maps will be spatially normalized to the standard MNI space by using the transformation fields derived from tissue segmentation of structural images and resampled to 3 mm isotropic voxels.

#### BOLD data

RS-BOLD data will be preprocessed in the toolbox of MATLAB (Data Processing Assistant for Resting-State fMRI, DPARSF; http://www.restfmri.net/forum/DPARSF). SPM8, RS-fMRI data analysis toolkit (REST1.6; http://www.restfmri.net) and graph-theoretical network analysis (GRATNA; https://www.nitrc.org/projects/gretna) will also be selected to deal with the images. The first 10 time points will be discarded to ensure stable magnetization and allow the participants to adapt to the EPI scanning environment. After that, slice timing and head motion will be conducted, and scans with head motion of translation > 3.0 mm or rotation > 3° will be excluded. The functional images will then be spatially normalized to Montreal Neurological Institute (MNI) space using the transformation fields derived from tissue segmentation of individual structural images and resampled to 3 × 3 × 3 mm^3^. The resulting images will be smoothed with 8 mm FWHM isotropic Gaussian kernel. Linear trends will be removed from the image time series, and data will be band-pass filtered at 0.01–0.08 Hz. Finally, nuisance signals such as 24-parameter head motion profiles, white matter, and cerebrospinal fluid signals will be regressed out from each voxel’s time series to exclude non-neuronal sources [28].

Amplitude of low frequency fluctuation (ALFF), regional homogeneity (ReHo) and functional connectivity (FC) values will be estimated in the DPARSFA software that is developed to extract abnormal regions between two groups. Small-world properties and network efficiency will be calculated in the GRETNA software to compare the topological characteristics between two groups.

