#### Functional and perfusion parameters

Both voxel-based and ROI-based 2-sample Student-t test will be applied to compare global ReHo, ALFF/fALFF, CBF between susceptible group and healthy control group with age, sex, education and BMI as covariance. The reference time series for headache-related seed regions will be acquired by averaging the time series for all voxels within them. Correlations of this time-series will be calculated to measure FCs among these regions in each participant. To evaluate group differences in the resting-state topological properties, nonparametric permutation tests were applied [29]. Initially, we will calculate the between-group differences of the mean values for each topological property. Next, an empirical distribution of the difference will be obtained by randomly reallocating every property value into two groups and recomputing the mean differences between the two randomized groups (5,000 permutations) to test the null hypothesis that the observed group differences only occurred by chance. The 95th percentile points of each distribution will be used as critical values for a two-tailed test to determine whether the observed group differences could occur by chance. Non-parametric Spearman correlation will also be performed to delineate a possible relationship between functional alterations and clinical data as well as perfusion alterations and clinical data. Significance threshold will be set at *P* < 0.05 (FWE corrected).

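### BOLD head motion is handled only within each scan; the stated group comparisons of ReHo, ALFF/fALFF and network topology carry no motion summary, so residual motion could confound these secondary outcomes

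*Protocol article*

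**What the plan says.** Protocol article, Imaging data processing, BOLD data: after a head-motion step, "scans with head motion of translation > 3.0 mm or rotation > 3° will be excluded". The images are then normalised and "resampled to 3 × 3 × 3 mm^3". As the last preprocessing step, "nuisance signals such as 24-parameter head motion profiles, white matter, and cerebrospinal fluid signals will be regressed out from each voxel’s time series".

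Protocol article, Statistical analysis, Functional and perfusion parameters: voxel-based and ROI-based two-sample tests will "compare global ReHo, ALFF/fALFF, CBF between susceptible group and healthy control group with age, sex, education and BMI as covariance". Topological properties are compared by a permutation test that works by "randomly reallocating every property value into two groups and recomputing the mean differences between the two randomized groups (5,000 permutations"). No covariate is named for that test. For functional connectivity (FC), the section says how it is calculated in each participant but sets out no group model.

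None of the statistical sections mentions a comparison of motion between the two groups. Under Outcomes measure, all BOLD measures are secondary; the primary outcome is white matter integrity.

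**The concern.** Regressing motion parameters out of a voxel's time series acts within one scan. It removes the part of the signal that is linear in those parameters. It does not ensure that women who moved more and women who moved less end up with comparable ReHo, ALFF or network values, and the groups are compared at that between-woman level.

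The comparison is not randomised. Patients come from a pain clinic and controls are community women without headache, so nothing in the design balances motion. If patients lie less still during the scan of about six minutes, a motion effect could be read as a functional or topological abnormality of migraine. Such a parameter could also be carried into the ROC step under Correlation analysis, which takes forward the most sensitive parameters.

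The listed covariates do not cover this. Sex is constant because only females are eligible (Subject section), and age, education and BMI are not measures of motion.

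**Working it through.** **1. What acts at which level**

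| Step | Level | Contains a motion measure? |
|---|---|---|
| Head-motion processing, 24-parameter regression | within scan | yes |
| Exclusion above 3.0 mm or 3° | whole scan, yes/no | yes, gross motion only |
| ReHo, ALFF/fALFF group tests | between women | no: age, sex, education, BMI |
| Topology permutation test | between women | no: raw values reallocated |
| FC group comparison | between women | no model set out |

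**2. The exclusion limit**

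The translation limit of 3.0 mm equals one edge of the 3 mm resampled voxel. The stated acquisition grid ("FOV = 240 × 240 mm^2^, matrix = 64 × 64, slice thickness = 3 mm, in-plane spatial resolution = 3 × 3 mm^2") implies 240/64 = 3.75 mm in-plane, which does not agree with the 3 mm in the same sentence; against 3.75 mm the limit is 3.0/3.75 = 0.8 of a voxel.

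The rotation limit is an angle. Displacement = radius × 3 × π/180, which gives 2.6 mm at 50 mm, 3.0 mm at 57.3 mm and 4.2 mm at 80 mm (radii assumed). So the limit removes gross motion but leaves a range of motion among the retained scans.

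**3. Possible size**

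The plan gives no figure to reproduce here. Two inputs are missing from the documents and are assumed:
- dm, the difference in motion between groups, in SD;
- r, the correlation of residual motion with the BOLD measure after the 24-parameter regression.

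Spurious standardised difference: δ = dm × r. With no true difference, the two-sided rejection rate at 0.05 comes from the non-central t distribution with 2n − 2 degrees of freedom and non-centrality δ × √(n/2). The group sizes are those in the Subject section: 40 per group for the power statement, 55 enrolled.

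| dm | r | δ | n = 40 | n = 55 |
|---|---|---|---|---|
| 0.2 | 0.1 | 0.02 | 5.1% | 5.1% |
| 0.3 | 0.3 | 0.09 | 6.8% | 7.5% |
| 0.5 | 0.3 | 0.15 | 10.2% | 12.2% |
| 0.5 | 0.4 | 0.20 | 14.3% | 18.0% |
| 0.8 | 0.5 | 0.40 | 42.4% | 54.7% |

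Example: δ = 0.20 and n = 40 give non-centrality 0.20 × √20 = 0.894 on 78 degrees of freedom, and a rejection rate of 14.3%.

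These are rates for one unadjusted test. The plan's threshold is FWE-corrected and partly voxel-based, so they are not the error rates of the planned maps. FWE correction controls chance error over many tests; it does not remove a systematic shift.

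**4. Cost of the covariate**

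With equal groups, a motion difference of dm SD gives a squared correlation between group and motion of dm²/(dm² + 4). The variance of the group contrast is then multiplied by 1 + dm²/4. At dm = 0.5 this is 1 + 0.25/4 = 1.0625, about 6%, before any gain from lower residual variance.

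**The case against.** The strongest defence is that motion is already handled in several places: foam padding, the instruction to lie quietly, a head-motion step, exclusion of gross motion, and regression of 24 motion parameters with white matter and CSF signals. Nothing in the documents says that women with migraine move more, or that a correlation of motion with the BOLD measures survives that regression. The lowest row of the assumed range is practically no bias. This stands, and it limits the point to possible residual motion.

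It can also be said that an article may leave model detail to a fuller document. That holds for FC, where no group model is given, so no error can be charged there. It does not hold for ReHo and ALFF/fALFF, whose covariate list is stated, or for topology, where the article describes a permutation of raw values.

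A third objection is that adjusting for motion is not free. If motion differs by group, the covariate is correlated with group; if restlessness belongs to the condition, adjustment may remove some true difference. This stands, and is why both sets of results should be shown.

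Two stronger readings are tempting. A reader might infer that the exclusion limit is itself the fault because it equals a whole voxel. That is exact only for translation on the resampled grid; for rotation it needs a radius near 57 mm. Nor are the retained scans left uncorrected. A reader might also infer that the BOLD findings will be motion artefacts. Without motion data, the documents do not support that.

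**Conclusion.** The point holds as a limited one. The stated group comparisons of ReHo and ALFF/fALFF, and the permutation test of topology, include no between-woman motion measure, and no comparison of motion by group is mentioned. Residual motion could therefore confound these comparisons if patients and controls differ in it.

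The size cannot be derived from the documents. Under moderate assumptions (δ from 0.09 to 0.20 SD), a single uncorrected 5% test with 40 per group would reject falsely about 7% to 14% of the time; over the wider assumed range the rate runs from 5.1% to 42.4%. Only secondary outcomes are affected; the primary diffusion outcome is not touched. This is an inexpensive improvement, not a defect that undermines the trial.

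**What to change.** - Keep the exclusion rule as it is.
- Compute mean framewise displacement for each woman from the realignment parameters that the head-motion step and the 24-parameter regression already require.
- Report it by group.
- Replace sex, which is constant in this sample, with mean framewise displacement in the covariate list for ReHo and ALFF/fALFF, and include it in any FC group comparison.
- For topology, permute covariate-adjusted residuals in place of raw values. This alters the described test rather than adding one term to it.
- Show results with and without the motion term.

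The cost is no new scans or participants, one degree of freedom, and about 6% more variance in the group contrast if motion differs by 0.5 SD. Some true group difference may be removed if motion is related to the condition. The covariate brings the false-positive rate back to about 5% only if the relation is roughly linear and motion is well measured.

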#### Secondary outcomes measure

Headache level (1–10, VAS), volumetric characteristics (e.g. GMV atrophy), functional characteristics (e.g. ReHo, ALFF/fALFF and FC and abnormalities), topological properties (e.g. small-world properties and network efficiency) and perfusion properties (e.g. CBF changes).

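### The single BOLD processing order leaves fALFF without its meaning and lets the smoothing kernel create much of ReHo, so each metric needs its own stated input

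*Protocol article*

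**What the plan says.** The BOLD data section of the protocol article describes preprocessing as a sequence. After normalisation and resampling to 3 mm voxels comes smoothing, followed directly by detrending: "The resulting images will be smoothed with 8 mm FWHM isotropic Gaussian kernel. Linear trends will be removed from the image time series". The same sentence goes on to the filter: "Linear trends will be removed from the image time series, and data will be band-pass filtered at 0.01–0.08 Hz". Nuisance regression closes the sequence: "Finally, nuisance signals such as 24-parameter head motion profiles, white matter, and cerebrospinal fluid signals will be regressed out from each voxel’s time series".

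The next paragraph turns to the metrics: "Amplitude of low frequency fluctuation (ALFF), regional homogeneity (ReHo) and functional connectivity (FC) values will be estimated in the DPARSFA software". It gives no metric an input of its own.

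fALFF is not named in that section. It appears under Functional and perfusion parameters, where the plan is to "compare global ReHo, ALFF/fALFF, CBF between susceptible group and healthy control group", and among the secondary outcomes: "functional characteristics (e.g. ReHo, ALFF/fALFF and FC and abnormalities".

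The 3D-pCASL data section works the other way round: the CBF image is derived first and smoothed last.

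**The concern.** Two of the named functional outcomes depend on a property of the data that an earlier step has already changed.

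- **fALFF** is, in its usual definition, the amplitude in the low-frequency band divided by the amplitude over the whole frequency range. A band-pass over that band removes what the denominator is meant to hold.
- **ReHo** is the concordance of a voxel's time series with those of its neighbours. Smoothing makes neighbouring voxels share signal before their concordance is measured.

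The position of nuisance regression adds a third question. Regressors that still contain out-of-band variation, fitted to filtered data, put some of that variation back. At stake is whether the group comparisons of fALFF and ReHo can be read as what their names say.

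**Working it through.** The article gives no figure for this point, so there is none to reproduce. The check applies the stated order to synthetic data with the article's own settings.

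**Inputs**
- TR 2 s and scan time 6 min 10 s (RS-bold section): 370 / 2 = 185 volumes. Less 10 discarded (BOLD data section): 175 volumes. Highest frequency: 1 / (2 × 2) = 0.25 Hz.
- Band 0.01–0.08 Hz, kernel 8 mm FWHM, voxels 3 mm, and 24 motion + white matter + CSF = 26 regressors (BOLD data section).
- Assumptions: an ideal filter; white noise plus a 1/f component of relative strength 0 to 2; regressors that behave like a random walk plus noise; the fALFF band equal to the filter band.

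**fALFF**

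fALFF = Σ A(f) over 0.01–0.08 Hz ÷ Σ A(f) over 0 < f ≤ 0.25 Hz.

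The frequency step is 1 / (175 × 2) = 0.00286 Hz. That gives 87 bins above zero, of which bins 4 to 28, that is 25, lie in the band. White noise should give about 25 / 87 = 0.287, and the simulation gives 0.288. After the band-pass the other 62 bins are empty, so numerator and denominator are the same sum and the ratio is 1.

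| 1/f strength | Proper fALFF: regressed, not filtered (SD) | After band-pass | Then in-band regressors | Then unfiltered regressors (SD) | Out-of-band power in that last case | Correlation of that last case with proper fALFF |
|---|---|---|---|---|---|---|
| 0 | 0.288 (0.025) | 1.0000 | 1.0000 | 0.621 (0.038) | 0.135 | 0.34 |
| 0.5 | 0.306 (0.026) | 1.0000 | 1.0000 | 0.626 (0.037) | 0.130 | 0.37 |
| 1 | 0.333 (0.028) | 1.0000 | 1.0000 | 0.632 (0.037) | 0.124 | 0.37 |
| 2 | 0.364 (0.031) | 1.0000 | 1.0000 | 0.635 (0.038) | 0.119 | 0.35 |

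The SD after the band-pass is below 1e-16. A separate run with unfiltered regressors gave about 0.67 and a correlation of 0.26. So fALFF is either constant or, at about 0.6 to 0.7, mostly a product of the regressors.

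**ReHo**

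ReHo = Kendall's W = 12 Σ(Rₜ − R̄)² ÷ [K²(T³ − T)], with K = 27 voxels, T = 175 time points and Rₜ the rank sum at time t. The kernel SD is 8 / 2.3548 / 3 = 1.13 voxels. Independent noise should give about 1 / 27 = 0.037.

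| Intrinsic smoothness (FWHM) | Unsmoothed | Band-pass only | 8 mm smoothing | 8 mm smoothing, then band-pass |
|---|---|---|---|---|
| 0 mm (pure noise) | 0.037 | 0.038 | 0.499 | 0.494 |
| 4 mm | 0.084 | 0.084 | 0.544 | 0.543 |
| 6 mm | 0.182 | 0.183 | 0.609 | 0.609 |

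The rise comes from the kernel, not the filter. Two other runs gave 0.48 and 0.49 for smoothed noise.

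In a simulated pair of regions with a true difference, unsmoothed ReHo was 0.223 and 0.506, a gap of 0.283. After smoothing it was 0.820 and 0.938, a gap of 0.118. The ordering survives, but the gap falls to 0.118 / 0.283 = 42% of its size.

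**The case against.** The strongest defence is that a journal article condenses the pipeline. The BOLD data section does not name fALFF, and the software may take a different input for each metric. This would carry weight if the article had left the order open. It states an order, closes it with nuisance regression and then lists the metrics. If the software is to branch, the text has to say so. The perfusion section shows that the article can place smoothing after a derived map when it means to.

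Four stronger readings are tempting, and the documents do not support them.

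- **fALFF is fixed at 1.00 and its group differences also come from reinserted motion.** These exclude each other. In-band regressors keep the ratio at 1.00 and reinsert nothing. Unfiltered ones reinsert out-of-band power and move it off 1.00.
- **The regressors are unfiltered.** The article does not say so. White matter and CSF signals taken from already filtered images would be in-band. The harm from the late regression step is therefore conditional, and with identically filtered regressors it disappears.
- **ReHo shows the kernel instead of brain activity, or favours one group.** Ordering and part of the contrast survive smoothing. In another simulation, smoothed and unsmoothed ReHo still correlated 0.59 to 0.81 across subjects, although the standardised group difference fell (0.36 to 0.11, 0.62 to 0.10 and 0.37 to 0.30 in three settings). The same kernel applies to both groups, so no direction of bias follows.
- **ALFF is spoiled too.** ALFF is an in-band amplitude, and an ideal band-pass over the same band leaves it unchanged.

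**Conclusion.** The point holds for fALFF and ReHo as the order is written. That fALFF becomes about 1.00 after the band-pass follows from its definition, and a real filter would come close to the ideal one. The alternative of about 0.6 to 0.7, with a correlation of about 0.26 to 0.37 with proper fALFF, rests on unfiltered regressors and synthetic signals. In neither case can the result be read as fALFF.

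For ReHo, the kernel alone lifts pure noise from about 0.04 to about 0.48 to 0.50. The cost is compressed contrast and lost local specificity in both groups, of a size that depends on the signal model.

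A reader might infer that the trial's main result is at risk. It is not: the primary outcome is white matter integrity from DKI, which this pipeline does not touch. The point should be fixed, but it is limited to secondary outcomes.

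**What to change.** Replace the single sequence in the BOLD data section with a stated input for each metric:

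- Nuisance regression before band-pass filtering, or with regressors filtered in the same way as the data.
- fALFF from nuisance-regressed data that have not been band-passed. Taking ALFF from the same data keeps the two consistent, although no harm to ALFF has been shown.
- ReHo from filtered, unsmoothed data, with the ReHo map smoothed afterwards.
- FC and the network time series from the filtered data.

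Name fALFF in that section, since it is tested and listed as an outcome. The cost is a changed order of processing steps and a few sentences of text. No new scans are needed, and raw data already collected can be reprocessed.
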